## Abstract

**Background:**

The risks associated with gestational diabetes mellitus (GDM) are well recognized, and there is increasing evidence to support treatment of the condition. However, clear guidance on the ideal approach to screening for GDM is lacking. Professional groups continue to debate whether selective screening (based on risk factors) or universal screening is the most appropriate approach. Additionally, there is ongoing debate about what levels of glucose abnormalities during pregnancy respond best to treatment and which maternal and neonatal outcomes benefit most from treatment. Furthermore, the implications of possible screening options on health care costs are not well established. In response to this uncertainty there have been repeated calls for well-designed, randomised trials to determine the efficacy of screening, diagnosis, and management plans for GDM. We describe a randomised controlled trial to investigate screening uptake rates and the clinical and cost effectiveness of screening in primary versus secondary care settings.

**Methods/Design:**

This will be an unblinded, two-group, parallel randomised controlled trial (RCT). The target population includes 784 women presenting for their first antenatal visit at 12 to 18 weeks gestation at two hospitals in the west of Ireland: Galway University Hospital and Mayo General Hospital. Participants will be offered universal screening for GDM at 24 to 28 weeks gestation in either primary care (n = 392) or secondary care (n = 392) locations. The primary outcome variable is the uptake rate of screening. Secondary outcomes include indicators of clinical effectiveness of screening at each screening site (primary and secondary) including gestational week at time of screening, time to access antenatal diabetes services for women diagnosed with GDM, and pregnancy and neonatal outcomes for women with GDM. In addition, parallel economic and qualitative evaluations will be conducted. The trial will cover the period from the woman’s first hospital antenatal visit at 12 to 18 weeks gestation, until the completion of the pregnancy.

**Trial registration:**

Current Controlled Trials: ISRCTN02232125

## Background

Gestational diabetes mellitus (GDM) has been defined by the World Health Organization (WHO) as hyperglycaemia of variable severity with onset or first recognition during pregnancy [1]. The risks associated with gestational diabetes mellitus are well recognized. Pregnancies complicated by GDM are associated with increased incidence of both adverse maternal outcomes (pregnancy-induced hypertension, polyhydramnios and caesarean section) and neonatal outcomes (prematurity, large for gestational age, neonatal unit admission, neonatal hypoglycaemia and respiratory distress) [2,3]. Later in life, both the mother and child are at increased risk of hospital admission, obesity, type 2 diabetes and heart disease [2,4-7]. Fortunately, these complications seem to be lessened by better detection and management of the condition [8,9].

There is a lack of robust evidence relating to the prevalence of GDM internationally [10,11]. This is due in large part to the use of a wide range of definitions and diagnostic criteria [12-14], as well as variations in prevalence across regions and ethnic groups [10,15].

Nonetheless, there is evidence that GDM affects significant numbers of pregnancies each year and that the prevalence of GDM has been increasing rapidly in recent years [16]. In Ireland, a large-scale research study funded by the Health Research Board and conducted by the Atlantic Diabetes in Pregnancy (Atlantic DIP) consortium, found that 12.4% of pregnancies in Ireland are complicated by GDM [17] according to the IADPSG (International Association of Diabetes and Pregnancy Study Group) diagnostic criteria [12].

Despite the increasing prevalence of the disease and the adverse consequences associated with it, there is still significant uncertainty about the screening, diagnosis and management of GDM [10,15].

In terms of screening, for example, professional groups disagree on whether to recommend universal or selective screening (based on risk factors) [12,18,19]. While some studies have found that universal screening for GDM is superior to risk factor-based screening in terms of number of cases detected, time to diagnosis and treatment, and improved pregnancy outcomes [20,21], others have found no such effects. For example, a review of four trials comparing universal and selective screening, found that there is little high-quality evidence on the effects of screening for GDM on health outcomes for mothers and their babies. The paper concluded that further research is required to see which recommendations for screening practices for GDM are most appropriate [22].

Additionally, the site of screening is likely to be important, both in terms of the location of the screen (regional versus local) and in terms of the provider of the screening service (GP versus hospital). For example The Atlantic DIP study, which offered universal screening to all pregnant women, recorded an uptake rate of only 44% [17]. Follow-up analysis to explain this low screening uptake rate revealed that travel distance to the hospital screening site is an important factor in determining uptake rates [23]. Specifically, the probability of attending for screening is 15% lower for a patient who lives 50 kilometers from a screening centre, compared to an otherwise similar patient who lives closer to the hospital. The corresponding reduction in the probability of attending for an individual residing 100 kilometers away is 30%. This suggests that the availability of GDM screening in local (primary care) settings could result in higher uptake rates; however, this has not been empirically tested to date.

It is possible that service provider differences may impact on uptake rates too. Given that the oral glucose tolerance test (OGTT) screen involves three blood draws and takes in excess of two hours to complete, it is conceivable that factors such as wait time, space and comfort in the waiting area, and perceived skill of the phlebotomist/nurse/GP, may influence the decision to attend. However, to date, no evidence exists on this issue. Additionally, evidence is needed in order to determine if the site of GDM screening will impact health outcomes; It is possible that there may be differences between primary and secondary care in terms of timeliness of screening, access to results, communication of results to patients, or access to GDM treatment for those with positive test results.

There is also a lack of consensus surrounding which pregnancy outcomes can be influenced by GDM management. Earlier published work found little evidence for an effect of treatment on various perinatal outcomes [24,25]. A 2003 Cochrane Collaboration systematic review also concluded that 'there are insufficient data for any reliable conclusions about the effects of treatments for impaired glucose tolerance on perinatal outcomes’ [26]. However, more recent evidence has shown a beneficial effect of treatment. For example, in a RCT comparing GDM treatment versus routine care for mildly diabetic patients (that is, those not having overt diabetes), Crowther [8] found that treatment for GDM reduced the rate of serious perinatal outcomes (death, shoulder dystocia, bone fracture, and nerve palsy) from 4% to 1%. Rates of caesarean section delivery were similar in the two groups. On the other hand, another study [27] showed no significant difference in a combined endpoint analysis between treated and untreated women, although treatment did lower the risks of fetal overgrowth, shoulder dystocia, caesarean delivery and pre-eclampsia. Recent meta-analyses have shown treatment effects for some perinatal complications - for example, shoulder dystocia, large for gestational age (LGA) and macrosomia in the infant, and pre-eclampsia in the mother [28-30]. Thus, while the evidence is mounting for the benefits of treatment there is still uncertainty about which outcomes can be influenced and, moreover, what degree of carbohydrate intolerance will benefit most from treatment [28,31]. In response to this uncertainty there have been repeated calls for well-designed, randomised trials to determine the efficacy of screening, diagnosis, and management of GDM.

### Screening in Ireland

In Ireland, although guidelines exist, there is no nationally implemented screening policy for GDM. However, the Atlantic DIP network^a^[1] advocates a universal screening approach for all pregnant women [17]. Part of the rationale for this policy is that research has shown that implementation of selective screening would decrease the number of screens by only 10% while adding significantly to the complexity of the screening process [32]. Currently in Ireland, GDM screening is only offered at secondary care sites. Limiting screening to hospital sites can result in geographical inequalities in access to screening. Additionally, since screening for GDM facilitates the identification of women who are at risk of developing type 2 diabetes in the future and who should undergo long-term health surveillance and preventative measures, women residing in more remote locations are more disadvantaged in terms of both their short- and long-term health.

Thus, it is important to understand if offering a screening programme in primary care would improve uptake rates, access to treatment and pregnancy outcomes. Finding answers to these questions could have important implications for the planning and provision of future GDM screening services nationally. The challenge to the health service is to provide a screening programme that accurately identifies the population at risk and is able to ensure that the uptake rate in the population at risk is on par with international norms for screening programmes. In order to do this, evidence is required on the clinical and cost effectiveness of alternative screening models that could be introduced. A primary versus secondary care based universal screening programme for GDM has not been previously explored or evaluated.

In this paper, we detail an RCT to compare the relative clinical and cost effectiveness of a primary versus secondary care based universal screening programme for GDM. The primary outcome variable is screening uptake rate at each site. Secondary outcomes include gestational age at time of screen, timing of access to antenatal diabetes care services for women with GDM, and pregnancy outcomes for women with GDM. In parallel, we will investigate the cost implications of primary versus secondary care screening. We will also conduct a qualitative analysis of user and stakeholder attitudes, preferences, barriers and facilitators of screening at each site.

#### Objectives

The aim of the trial is to assess the uptake, clinical and cost effectiveness of universal screening for GDM in primary care versus secondary care locations.

### Hypothesis

The formal null hypothesis to be tested in this study is that there is no difference in uptake of screening for GDM amongst women randomised to primary care screening compared to women randomised to secondary care screening.

## Methods/Design

### Unblinded, parallel group, randomised controlled trial

A randomised controlled trial will be conducted to compare the uptake, clinical effectiveness and cost effectiveness of universal screening for GDM in primary versus secondary care. The CONSORT guidelines [33] for the conduct of RCTs will be employed in the design and analysis of the trial. The trial is registered with the International Standard Randomised Controlled Trial Number, ISRCTN02232125.

### Interventions

All women who consent to participate in the study will be invited for a 2-hour, 75 g, oral glucose tolerance test (OGTT) at between 24 to 28 weeks gestation. Participants will be randomised into either the primary care screening group or the secondary care screening group. The scheduling process differs slightly between groups. In the primary care group, the GP is requested to schedule the OGTT screening appointment with the woman; in the secondary care group researchers schedule the screening appointment during the recruitment phone calls. In neither group is the responsibility for scheduling the appointment left to the woman.

Primary care screening group: All women randomised to the primary care screening group will be offered a screening appointment for GDM at their local general practitioner (GP) clinic. Following randomisation, a study information leaflet and the materials required to perform an OGTT will be sent to the woman’s GP by the research team. The GP is requested to contact the woman in order to schedule the OGTT appointment at 24 to 28 weeks gestation. As per usual care, the GP will send the test samples to the local laboratory for analysis. Following analysis, the laboratory will send the test results directly to the GP and the GP will inform the woman of her result. For positive test results, the GP will be directed to contact the local maternity unit to make an appointment for the woman to be seen at the diabetes antenatal service.

Secondary care screening group: All women randomised to the secondary care screening group will be offered a screening appointment at the hospital site. Following randomisation, the study researcher will schedule the appointment for the OGTT screen and send the list of OGTT appointments to the maternity unit, for inclusion in their OGTT appointment diary. As per usual care, the test samples will be sent to the local laboratory for analysis. Following analysis, the laboratory will send the test results directly to the consulting obstetrician, who in turn informs the woman of her result. For positive test results, an appointment will be made by the midwife for the woman to attend the antenatal diabetes service.

#### Setting

This study will run concurrently at two sites: Galway University Hospital (GUH) and Mayo General Hospital (MGH) and their associated network of general practitioner (GP) clinics and primary care teams. GUH is the lead Atlantic DIP network site with approximately 4,000 deliveries per year. GUH serves both urban and rural populations, including Galway city, the third largest city in Ireland. MGH serves a rural population and has approximately 2,300 deliveries per year. Thus, GUH and MGH patients can be considered as broadly representative of the general population of Ireland. Within this geographical region is a network of general practitioners (Western Research and Educational Network: WestREN) who are interested in pursuing research in the community in collaboration with colleagues in secondary care. WestREN includes more than 80 general practices and more than 400,000 patients along the western seaboard of Ireland. Recently published research confirms that the WestREN practices and patients are representative of Ireland generally [34].

In advance of the commencement of the trial, all GPs in the Galway and Mayo region will be sent a trial information leaflet and asked to formally opt-out if they do not wish to participate. Additionally, GPs will be instructed to inform the study team if they are unable to perform the OGTT test, in such circumstances the participant will be offered a screen in secondary care.

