#### Eligibility criteria

•Inclusion criteria: Women presenting with a pregnancy at GUH and MGH during the recruitment phase will be included.

•Exclusion criteria: Women with established diabetes or diagnosed GDM will be excluded.

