#### Recruitment

Recruitment for the trial will be initiated at the woman’s first hospital visit at 12 to 18 weeks gestation. A list of all women with a confirmed pregnancy presenting at the obstetrics outpatient clinics at GUH and MGH will be obtained from the hospital databases by the principal investigator, who is a member of the clinical care team at both sites. Each woman will be sent an invitation letter, participant information leaflet and participant consent form in the post. The information will be followed up with a phone call to each woman to answer questions and obtain verbal consent before randomising those who consent to the primary care and secondary care screening groups. The baseline characteristic questionnaire will be administered at this time. The phone calls will be conducted by members of the research team. Each consenting woman will be asked to return the written consent form to the study office. For some of the participants (that is, those who meet the risk factor criteria for selective GDM screening), an appointment for an OGTT may have already been scheduled at their 12 to 18 week hospital visit. In such cases, researchers will continue the randomisation process as usual and inform the clinic if a change is required to the screening schedule. Those who were not selected for screening at the 12 to 18 week clinic but who consent to the study and are randomised into the secondary care screening group will be added to the hospital’s screening schedule. Outcome data will not be collected from participants who discontinue. The flow chart in Figure 1 represents the movement of a participant through the stages of recruitment.

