#### Randomisation

The randomisation process in this RCT will use random permuted blocks to ensure similar numbers of participants in each intervention arm throughout the trial and equal numbers in each arm by the end of the study. Blocks of varying length will be used to reduce the predictability of the allocation sequence. In advance of participant recruitment, an independent researcher will be responsible for generating the allocation sequence using the NQuery statistical software program (version 2.0). (Statistical Solutions, Cork, Ireland; http://www.statistical-solutions-software.com) Sealed envelopes will be used to assign participants to intervention groups. Thus, the allocation sequence will be concealed from all study researchers until the interventions are assigned.

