### Outcomes

#### Primary outcome: uptake of screening

The primary outcome in the RCT is uptake of screening in the primary care and secondary care settings. First, the number of screening offers accepted will be assessed by comparing the number of screens offered (via the obstetrics outpatient clinic list) with the number of offers accepted (via the randomisation schedule). Second the uptake rate will be determined by comparing the number of women randomised to each setting to the number of OGTTs performed in that setting (via the GUH and MGH laboratory records).

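### As written, nothing keeps a woman whose GP opted out before the trial from being randomised to primary care screening, where the uptake count could score her only as a failure

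*Protocol article*

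**What the plan says.** All places are in the Protocol article.

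- **Setting.** Ahead of the trial, GPs in the Galway and Mayo region receive a leaflet and are "asked to formally opt-out if they do not wish to participate". A separate sentence covers GPs who are unable to perform the test: "in such circumstances the participant will be offered a screen in secondary care".
- **Eligibility criteria.** "Women presenting with a pregnancy at GUH and MGH during the recruitment phase will be included". The only exclusion is: "Women with established diabetes or diagnosed GDM will be excluded". The woman's GP is not mentioned.
- **Recruitment.** Women are taken from the hospital lists: "Each woman will be sent an invitation letter, participant information leaflet and participant consent form in the post". Those who consent by telephone are randomised.
- **Randomisation.** "The randomisation process in this RCT will use random permuted blocks", of varying length, with sealed envelopes. No check of GP status and no stratification by it is described.
- **Interventions.** Every woman allocated to primary care is to be offered a test at her own GP clinic, and the GP is asked to arrange it.
- **Primary outcome.** The uptake rate is found by "comparing the number of women randomised to each setting to the number of OGTTs performed in that setting".
- **Analysis plan.** The main analysis is by intention to treat.

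**The concern.** GP opt-out is a baseline fact: it is collected before recruitment and can be looked up for each woman. The entry rules do not use it, so they admit a woman whose GP has declined the trial, and she may be allocated to a GP test that her GP has already said will not be offered. That conflicts with the Interventions section, which describes an offer made to everyone in the primary arm.

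The consequence falls on one arm. A primary-arm woman in this position counts among those randomised but cannot contribute a test in the primary care setting, even if she is tested in hospital. A secondary-arm woman with the same GP loses nothing. The stated hypothesis concerns uptake among women randomised to each arm. Part of the observed difference would then reflect GPs declining to take part in the trial, always to the disadvantage of primary care, and the trial would lose power for the difference it was sized to detect.

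**Working it through.** **Inputs from the Protocol article**
- Total sample 784, 80% power, 5% significance, change in uptake of at least 10% (Sample size and power calculation); 392 per arm (Abstract).
- 74% recruitment and 30% attrition, 1,513 invited (same section).
- Earlier uptake of 44% in the universal screening study (Background). The sample-size section states no baseline rate.

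**Assumed**
- Secondary-arm uptake 45%, primary-arm uptake 55% where the GP takes part; the 10% change is read as percentage points; two-sided test.
- f, the share of women whose GP has opted out. The document gives no figure, so a range is shown.

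**Step 1: reproduce the plan.** With p̄ = (p₁ + p₂)/2,

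n per arm = [1.96·√(2p̄(1−p̄)) + 0.842·√(p₁(1−p₁) + p₂(1−p₂))]² / (p₁ − p₂)²

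For 45% v 55% this is 391.3, rounded up to 392, so 784 in total. For 44% v 54% it is 391.1, also 392 and 784. Invitations: 784 / (0.74 × 0.70) = 1,513.5, against the stated 1,513. The sample size is sound on its own terms and contains no allowance for opted-out GPs.

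**Step 2: expected primary-arm uptake with opted-out GPs' patients included**
- Only tests in the allocated setting count: 0.55 × (1 − f).
- Tests in either setting count, and these women attend hospital at the secondary-arm rate: 0.55 × (1 − f) + 0.45 × f.

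**Step 3: power with n = 392 per arm**

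Power = Φ{ [|p₁ − p₂|·√n − 1.96·√(2p̄(1−p̄))] / √(p₁(1−p₁) + p₂(1−p₂)) }

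| Assumed f | In-setting uptake | Difference from 45% | Power | Either-setting uptake | Difference from 45% | Power |
|---|---|---|---|---|---|---|
| 0 | 55.0% | 10.0 points | 80% | 55.0% | 10.0 points | 80% |
| 2% | 53.9% | 8.9 | 70% | 54.8% | 9.8 | 78% |
| 5% | 52.25% | 7.25 | 53% | 54.5% | 9.5 | 76% |
| 10% | 49.5% | 4.5 | 24% | 54.0% | 9.0 | 71% |
| 20% | 44.0% | −1.0 | – | 53.0% | 8.0 | 61% |

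Under in-setting counting, the planned gain disappears at f = 1 − 0.45/0.55, about 18%. Starting from 44% v 54% changes little: in-setting power is 53% at f = 5% and 25% at f = 10%.

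**Step 4: no true difference.** If uptake were 44% in both arms wherever the test is offered, f = 10% under in-setting counting would produce a primary-arm deficit of 0.44 × 0.10 = 4.4 points. The test would then reject in about 24% of trials instead of 5%.

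**The case against.** A reader might infer that the trial will randomise these women and that its primary comparison is therefore biased. The document does not support that. No sentence says that patients of opted-out GPs are randomised, and the promise of a GP appointment to every primary-arm woman could mean that they are removed beforehand. The recruitment flow chart (Figure 1) is not available here and might show such a step. This stands: the point is about what the written rules allow, not about what will happen. Who may be randomised is nevertheless a matter for the eligibility criteria, and the published criteria have no such condition.

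A reader might also infer that these women are sent to hospital for their test. The hospital offer is written for GPs who are unable to perform it; what happens when a GP has opted out is not stated. This stands too. It does not rescue the in-setting count, because the woman scores as a failure whether or she is tested in hospital or not tested at all.

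The severe figures depend on the in-setting rule, which is a separate question of outcome definition, and the opt-out shares are assumed. Both are true, which is why both counting rules are tabulated.

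The strongest argument of principle is pragmatic: GP non-participation may be part of the effect of a primary care programme, and excluding these women narrows a population meant to be broadly representative. That is a legitimate estimand. But the Interventions section describes an offer to all women in the arm, and a GP who declines a research trial has not necessarily declined to provide a service. The planned per-protocol and sensitivity analyses are stated only in general terms and do not say how these women are treated.

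**Conclusion.** The concern holds in conditional form. GP opt-out is known before randomisation, the published entry rules ignore it, and the Setting, Eligibility criteria and Interventions sections need to be reconciled. If such women are randomised, the written uptake count produces a loss in the primary arm only.

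Its size cannot be fixed from the document. On the assumed 45% v 55%, in-setting power falls from 80% to about 53% at a 5% opt-out share and to about 24% at 10%. If tests in either setting count and these women attend at the hospital-arm rate, 10% leaves about 71%. With few opt-outs the effect is small. The correction is cheap and has to be made before randomisation, so it should be made.

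**What to change.** **Preferred.** Add to the eligibility criteria that the woman's GP has not opted out at the time of the recruitment call. Check the opt-out list for every woman before the envelope is opened, so that the restriction applies equally to both arms, and report the number excluded for this reason. Women whose GP proves unable to test after randomisation stay in their allocated arm under intention to treat.

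**Alternative, if the sponsor wants the pragmatic estimand.** Keep these women, record GP opt-out status at baseline in both arms, state whether hospital tests in the primary arm count as uptake, and add an analysis restricted in both arms to women whose GP had not opted out. Because that subgroup is defined before randomisation, the restricted comparison keeps the protection of randomisation.

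**Cost.** One eligibility line and one list check per woman. Under the preferred option the result applies to women whose GP had not opted out; reporting the number excluded keeps the opt-out information available for planning services.
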